#### Qualitative analyses

Qualitative data will be analysed using a framework approach [45–47]. This is a hierarchical, matrix-based method developed for applied qualitative research. It is particularly suited to research where the goals are clearly defined at the onset, for example, to support the development of a future trial. An initial thematic framework will be constructed from the interview objectives and existing literature (for example, literature on clinical trial recruitment and randomisation in research). The interview data will then be mapped onto this framework, and the framework will be amended if required to include new concepts introduced during the interviews. After all the data have been ‘charted’ in this manner, tables/matrices will be used to summarise each main theme and interpreted to address the interview objectives. Study participant interviews will be analysed in conjunction with the patient-partners. The draft thematic framework for the participant interviews will be fed back to the PPI steering group for their comments. We will incorporate their comments in the final analysis of the thematic framework. Elements of the thematic framework identified will be substantiated with anonymised participant quotes.

#### Quantitative analysis

For the quantitative data, we will use descriptive statistics (using the statistical software package SPSS version 21) to describe the outcomes, and to inform power and sample size calculations for a future definitive study. Based on the characteristics of the data, appropriate parametric or non-parametric statistics will be used. All tests will be two-sided with an alpha level of 0.05.

### Health economics evaluation

Descriptive analyses will be undertaken of both the EQ-5D™ responses (scored using the algorithm provided by the developers and the visual analogue scale scores) and SUQ data. Estimates of the cost of providing the intervention, the main cost drivers in terms of health care resource use, the impact of receiving the intervention prior to TKA on EQ-5D™ and quality adjusted life years will be presented. We will make estimates of the cost effectiveness of the intervention expressed as an incremental cost effectiveness ratio together with exploration of the impact of uncertainty. These analyses will be important for informing the main study data collection and the methodological challenges for undertaking a full economic evaluation.

### Assessment of safety and adverse events

The occurrence of adverse events as a result of participation within this study is not expected, since the trial involves the use of an evidence-based psychological intervention delivered by a suitably qualified psychologist. Therefore, no adverse event data will be collected. If a patient is identified as suicidal, usual clinical procedures will be followed by the clinical team responsible for the patient’s care.

If a potential participant is identified as having a high score on the HADS (>15) at baseline, we will recommend that they contact their GP to discuss this further. If a participant scores high on Question 9 on the BDI (‘I would kill myself if I had the chance’), a risk assessment will be undertaken, and we will advise them to discuss this score with their GP or contact the appropriate crisis team. This will not affect their participation in the study. If, however, they have been offered psychological therapy by routine NHS clinical services at the time of assessing eligibility, they will not be eligible for inclusion. In practice, this is unlikely, given the long waiting times for people to receive such therapies. If they are unable to participate in the trial treatment, this will indicate the upper limit of distress which may need to be applied as an exclusion criterion in future studies. In the unlikely event that a participant is found to have a suicidal risk, the recruiting NHS Trust’s standard suicide risk protocol will apply.

The patient-partners will have full UK Disclosure and Barring Service (DBS) clearance. Home visits will be conducted in accordance with our Trust’s lone working policy.

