There is a theoretical rationale, which is supported by research [4, 17, 18], for assuming that improving mood and attitudes towards surgery will result in better postoperative outcomes. For instance, studies have shown the relationship between psychological factors and wound healing, with higher anxiety and stress levels associated with greater postsurgical pain, and with pain having an effect on immune function and wound healing [17]; mood and attitudinal factors have been found to be associated with surgical outcomes, length of hospital stay, functional recovery, and patient self-report ratings of recovery [4]. However, the interventions used to address these psychological factors have been limited to ‘information giving’ preoperative classes [19–21]. None of these studies have examined the long-term impact of the intervention, nor have they examined mood-related pain and quality of life as outcomes. Furthermore, none of these studies have examined the cost-effectiveness of delivering psychological interventions in improving surgical outcomes.

Cognitive Behavioural Therapy (CBT) is a psychological treatment that has shown to be effective in treating depression and anxiety, and is considered a treatment of choice for these conditions by the National Institute for Health and Clinical Excellence [22]. TKA is a relatively costly intervention; based on the knee arthroplasty trial [23] on average, primary TKA and 5 years of subsequent care cost £7458 per patient (SD: £4058), although the benefits in terms of quality-adjusted life years (QALYs) are relatively large, with patients gaining an average of 1.33 (SD: 1.43) QALYs generating an incremental cost effectiveness ratio (ICER) of £5,623 per QALY gained [23, 24]. Improving the outcomes of TKA increases the value of the intervention to the patient and the NHS. However, there is limited research that demonstrates the clinical and cost-effectiveness of a short-term preoperative CBT-based intervention to improve postoperative TKA outcomes [25, 26]. Furthermore, there is limited research on patient-partner involvement in data collection and analysis in such studies. Therefore, evaluating this aspect within a feasibility trial may elucidate the potential challenges and benefits of such patient-partner engagement before attempting to implement this in a definitive trial.

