The WOMAC and ICOAP assess different aspects of pain. The ICOAP assesses intermittent and constant pain, whereas the WOMAC assesses pain, stiffness, and physical functioning. Possible score ranges for the ICOAP constant pain and intermittent pain subscales are 0 to 20 and 0 to 24, respectively, with higher scores indicating higher pain experienced. Possible ranges for the three WOMAC subscales are pain (0 to 20), stiffness (0 to 8) and physical function (0 to 68), with higher scores indicating more extreme pain, stiffness, and physical function limitations. The BDI and BAI are measures of the severity of mood disorder, and total scores range from 0 to 63 with higher scores suggesting severe depression or anxiety. The EQ-5D™ is a standardised instrument for use as a measure of health outcome. It is applicable to a wide range of health conditions and treatments; it provides a simple descriptive profile and a single index value for health status. The EQ-5D is primarily designed for self-completion by respondents and is ideally suited for use in postal surveys, in clinics, and face-to-face interviews. It is cognitively simple, taking only a few minutes to complete. Instructions to respondents are included in the questionnaire. The output from the questionnaire provides a simple descriptive profile and a single index value, which are used for health economic evaluation to enable estimation of quality adjusted life years. It is applicable to a wide range of health conditions and treatments. This study is using the five-level response category version. The ICOAP is recommended by the Osteoarthritis Research Society International, and has been Rasch analysed [36]. The Beck inventories are recommended in the Quality and Outcomes Framework guidance [37] and used extensively in OA research. These standardised assessments were selected because they have adequate psychometric properties, have been employed in other trials with this patient group, and map onto the areas our patient and public involvement (PPI) group felt were most important for people with knee OA. The SUQ is not a validated questionnaire but is based on standard practice and the resources available in the DIRUM database adapted for use in this study by health-economists, which includes the number and types of primary and secondary care NHS resources use (for example, (re)admissions, medication use, travel costs) and changes to employment status. The SUQ has been developed for the study to collect the use of NHS and social services resources by the participant during the study period.

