### Intervention group

The intervention group will receive up to 10 sessions of CBT, based on general principles of CBT for anxiety and depression, and pain management, tailored to the specific needs of each participant. This is not standardised as this is a feasibility trial, so we need the flexibility to determine what is appropriate. Participants will not all require the same number of sessions because they will not all have the same severity of problems. There are no standardised protocols for CBT for osteoarthritis or pre-surgical preparation for OA, so a key part of the feasibility trial is to establish the treatment protocol. The CBT sessions will be offered by a psychologist, trained in delivering CBT-based interventions, in the participant’s home or in clinic. Some participants prefer to be seen in hospital, and some prefer to be seen at home. As this is a feasibility trial, we plan to offer the flexibility to do either so we can determine what people generally prefer. In addition, due to disability issues, some participants may struggle to make it regularly to the clinic, and by offering home sessions, we are being more inclusive. Sessions will be once or twice weekly and last approximately one hour. The content of the intervention will combine the core elements of CBT for pain management outlined by Gatchel et al. [39], Morley [40], and the Gloucester Pain Management Manual [41], namely: psychoeducation on mood and pain (for example, pain processing, the relation between pain and stress, the CBT approach to self-management, etcetera); values-based goal-setting; self-management and behavioural activation (e.g. diet, exercise, activity planning, pacing, etcetera); relaxation and mindful breathing (including instruction on the fight/flight response); cognitive restructuring (including identifying negative automatic thoughts, changing negative thinking patterns, and challenging maladaptive beliefs); and post-surgical planning (for example, acceptance of rehabilitation time-scales and adaption of coping strategies). The therapy sessions will be audio recorded. These sessions will fit within the expected waiting time for surgery (18 weeks).

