### Criteria for terminating the study

The trial will not be terminated unless instructed by the funder, sponsor, or ethics committee, but failure to comply with treatment will be recorded as an outcome.

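### The protocol rules out all adverse event collection on an assumption it cannot then check, and the indirect harm signals it does gather in both arms are not designated or routed as safety data

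*Protocol article*

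**What the plan says.** In the protocol article, under Assessment of safety and adverse events, the premise is "The occurrence of adverse events as a result of participation within this study is not expected". The reason given is that the trial uses an "evidence-based psychological intervention delivered by a suitably qualified psychologist". The conclusion follows directly: "Therefore, no adverse event data will be collected". No arm, event type or degree of seriousness is exempted.

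The same section handles risk in individuals. A high HADS score leads to advice to see the GP. For a high score on BDI item 9, "a risk assessment will be undertaken, and we will advise them to discuss this score with their GP or contact the appropriate crisis team". The recruiting Trust's suicide risk protocol applies where needed.

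Other sections that bear on the rule:

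- **Intervention group:** "There are no standardised protocols for CBT for osteoarthritis or pre-surgical preparation for OA". The content is tailored to each participant, and establishing a treatment protocol is one of the trial's tasks. Sessions are to fit within an expected surgical wait of 18 weeks.
- **Participant feedback interviews:** sampling deliberately includes people who have complications, difficulties with therapy, or who drop out.
- **Baseline assessment, Participant outcome measures and Control group:** both arms complete the BDI, BAI, WOMAC, ICOAP, EQ-5D and service-use questionnaire (SUQ) at baseline and, by post, at 4 and 6 months. The SUQ covers admissions and readmissions, medication and any additional care.
- **Participants who withdraw:** withdrawal rates and any reasons offered are recorded, but leaving therapy is declared not to be a safety matter.
- **Criteria for terminating the study:** "The trial will not be terminated unless instructed by the funder, sponsor, or ethics committee".
- **Trial management:** an advisory group monitors progress. No flow of safety information is described.

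**The concern.** The rule treats events that are not expected as events that need not be looked for. The premise concerns events caused by participation, and causation by participation is exactly what a comparison of randomised arms would inform. Without recording in both arms, the premise can be neither supported nor refuted by the trial that relies on it.

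The setting makes this more than a formality. Participants are selected for anxiety or depression (a HADS subscale score above 7), and most are expected to have major surgery during follow-up. Some admissions and complications are therefore foreseeable in both arms whatever the therapy does.

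Three things are at stake. No adverse event rate could be reported for either arm. The bodies able to stop the trial are not shown to receive any safety information. And the definitive trial would inherit no tested procedure for recording harms. That last point is a missed opportunity rather than a failed aim, because harms collection is not among the listed objectives.

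**Working it through.** **1. Is this an omission or a decision?** The article gives a premise, a reason and a conclusion. It fixes the rule, so the gap cannot be put down to detail left for a fuller protocol or an analysis plan.

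**2. Does the reason carry the conclusion?** It has two parts: the therapy is evidence-based, and a qualified psychologist delivers it. Against the first stands the Intervention group section, which says this use of CBT has no standardised protocol and that the content will vary by participant. Against the expectation of no events stands the interview plan, which seeks out people with complications or therapy difficulties. Neither passage shows that the therapy causes harm. Together they mean that general evidence for CBT is a weak basis for not looking.

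**3. Does surgery fall inside follow-up?** The expected wait is 18 weeks, or 18 × 7 = 126 days. Six months is about 182 days. Since randomisation follows listing, surgery would usually precede the 6-month assessment. Postponement, which the Discussion anticipates, would change this for some participants.

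**4. What can already be seen by arm?**

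| Signal | Both arms? | Limitation as safety data |
|---|---|---|
| BDI (with item 9) and BAI change | Yes | Postal, at 4 and 6 months only; no worsening threshold stated |
| SUQ admissions and readmissions | Yes | Self-report; unvalidated; planned use is economic |
| Withdrawals and reasons | Yes | Reasons only where offered; therapy withdrawal declared not a safety matter |
| Losses to follow-up | Yes | Counted in the CONSORT diagram |
| Interviews | Yes, up to 30 participants | Purposive sample, so no rate can be derived |

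The first two depend on a returned questionnaire. Someone who has died or is seriously ill may return nothing and would be counted only as lost or withdrawn. Informal awareness would also differ by arm: CBT participants may have up to 10 therapist sessions, controls none.

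**5. How much would recording reveal?** The planned size reproduces: 2 × 25 = 50. It rests on a rule of thumb of 12 per group, so there is no power calculation to disturb.

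- *No events seen.* One-sided 95% upper limit: 1 − 0.05^(1/25) = 0.113, or 11.3% per arm. The two-sided exact limit is 1 − 0.025^(1/25) = 13.7%. For all 50 participants, one-sided: 1 − 0.05^(1/50) = 5.8%.
- *Chance of at least one event in an arm of 25*, 1 − (1 − p)^25. The documents give no event rate, so the risks p are assumptions:

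| Assumed true risk | Chance of at least one event |
|---|---|
| 1% | 22% |
| 2% | 40% |
| 5% | 72% |
| 10% | 93% |

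- *Comparing arms*, assuming 5% against 20% and a two-sided 0.05 level. With a pooled normal approximation, the null standard error is √(2 × 0.125 × 0.875 / 25) = 0.0935 and the alternative one is √((0.05 × 0.95 + 0.20 × 0.80) / 25) = 0.0911. Power = Φ((0.15 − 1.96 × 0.0935) / 0.0911) = Φ(−0.37), about 36%. The approximation is rough at such low expected counts, but the message is clear.

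Recording therefore buys coarse description and a tested procedure, not a comparison with useful power.

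**The case against.** The strongest reply is that the trial is not blind to harm. Both arms provide repeated mood and pain scores, self-reported admissions, use of additional care, and withdrawal reasons, and the SUQ data will be analysed descriptively. That stands. A reader might infer that nobody could see harm by arm at all; the documents do not support this, since worsening mood and self-reported admissions could be tabulated from planned data.

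A second reply is that the protocol does not contradict itself on evidence. The Abstract and Background statements concern benefit: "there is limited research that demonstrates the clinical and cost-effectiveness of a short-term preoperative CBT-based intervention to improve postoperative TKA outcomes". A reader might take them as undermining the safety claim, but they say nothing about safety, and the Background does call CBT effective for depression and anxiety, the conditions that qualify participants. That stands too. The tension lies with the unstandardised content and the planned interviews, and it weakens the rationale without refuting it.

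Third, individual safety is addressed by the HADS, BDI item 9 and suicide risk provisions. True, and nothing here questions them. They act on single participants and produce no summary by arm.

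Fourth, a reader might infer that the sponsor, funder and ethics committee will receive no safety information. The article does not say so. It describes no such route, and the full protocol may contain one. The narrower statement is the one made here.

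Finally, 25 per arm can reveal little, and the feasibility aims and sample-size inputs do not depend on these data. Both points hold, and they limit the severity. They do not justify a rule against recording, because description by arm needs no power.

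**Conclusion.** The point holds in a limited form. The protocol excludes all adverse event recording for a reason that its own design then leaves untestable. The remaining signals in both arms are real but indirect, depend largely on a returned questionnaire, and are neither designated as safety data nor described as going to those who can stop the trial. Serious events could pass as non-return or withdrawal.

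The size is modest. What is lost is a descriptive table by arm, in which no events among 25 would exclude rates above about 11% (one-sided 95%), together with experience of a recording procedure. The primary feasibility conclusions are unaffected. This should be fixed, but it is not a fatal flaw.

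The conclusion assumes that the sentence is followed as written, that 25 per arm are randomised and followed, and that surgery falls within follow-up for most participants. The risks used to illustrate detection and power are assumed.

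**What to change.** Replace the sentence excluding adverse event data with: *Serious adverse events (death, hospital admission other than for the planned knee surgery, self-harm or suicide attempt) will be recorded by the same enquiry in both arms up to 6 months after randomisation and tabulated descriptively by arm.*

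Add to the analysis:

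- Show these events beside SUQ admissions and readmissions, BDI item 9 responses, BDI and BAI worsening, and reasons for withdrawal or loss. Fix the worsening threshold before any results by arm are seen.
- Apply the same enquiry to people who do not return questionnaires, so that extra therapist contact does not create unequal ascertainment.
- Have someone other than the research associate prepare the by-arm table for the sponsor and advisory group. The research associate must stay blind (Minimisation of bias) but is also project manager (Trial management).
- Use medical notes only within the consent given. Informed consent describes access for diagnosis and other medical conditions, and follow-up use is a medication check where feasible. Confirm the scope before extracting events.
- Trial status reports 41 of the planned 50 already randomised. For these participants, state which data were obtained retrospectively.

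Reconcile the safety section with the interview plan, the SUQ description and the statement on therapy withdrawal. Existing clinical risk procedures are unchanged.

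The cost is an amendment, one log, one table and slight extra recording time. The sample size does not change, and the result must be presented as descriptive only.

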### Participants who withdraw

Participants will be informed that they are free to withdraw from the study at any time without it affecting their usual health care or legal rights. Participants will be withdrawn from the study if consent is withdrawn. However, they will be made aware that data collected before their withdrawal cannot be destroyed and may still be used in analysis but no identification will be possible. If a participant indicates a wish to withdraw from the intervention, we will enquire whether they will consider completing the primary outcomes. Participants who withdraw from the study will not be replaced, but withdrawal rates and reasons for withdrawal (where provided) will be recorded. Some participants may be unable to complete all therapy sessions. This information will be recorded.

Withdrawal from this therapy is not considered a safety issue for participants.

### Criteria for terminating the study

The trial will not be terminated unless instructed by the funder, sponsor, or ethics committee, but failure to comply with treatment will be recorded as an outcome.

### Trial management

A Trial Management Group (TMG) (TMG: [name], [name], [name], [name], [name], [name] and [name]) will meet fortnightly in the first 2 months and thereafter monthly to ensure that milestones are achieved. The progress of the study will be monitored by the Arthritis Research UK Pain Centre management group (who meet every 4 months), which is chaired by [name] and includes other members of the Pain Centre staff with clinical expertise in arthritis and pain. They have agreed to act as an advisory group. Finally, the progress of the study will also be reported to the PPI Advisory Panel at four meetings over the course of the study through one of our patient-partners on this study.

The RA will be project manager and will be supervised by the Chief Investigator (CI). The CI has overall responsibility for the study and shall oversee all study management.

